# A Cluster-Randomized Controlled Trial Evaluating the Effectiveness and Cost-Effectiveness of Tobacco Cessation on Prescription in Swedish Primary Health Care: A Protocol of the Motivation 2 Quit (M2Q) Study

**DOI:** 10.2196/resprot.6180

**Published:** 2016-09-16

**Keywords:** tobacco use cessation, primary health care, vulnerable populations, randomized controlled trial, pragmatic clinical trial, cost-effectiveness analysis, Sweden

## Abstract

**Background:**

In Sweden, the prevalence of tobacco use is disproportionately high among socioeconomically disadvantaged groups. Previous research and clinical experience suggest that prescribed lifestyle interventions in the primary health care (PHC) setting such as Physical Activity on Prescription are effective in changing behavior. However, there is a lack of evidence for if and how such a prescription approach could be effectively transferred into the tobacco cessation context.

**Objective:**

The aim of this trial is to evaluate the effectiveness and cost-effectiveness of Tobacco Cessation on Prescription (TCP) compared to current practice for tobacco cessation targeting socioeconomically disadvantaged groups in the PHC setting in Sweden.

**Methods:**

The design is a pragmatic cluster-randomized controlled trial. The sample will consist of 928 daily tobacco users with Swedish social security numbers and permanent resident permits, recruited from 14-20 PHC centers located in socioeconomically disadvantaged areas in Stockholm County. The primary outcome will be measured in self-reported 7-day abstinence at 6 and 12 months after the intervention. The secondary outcomes will be measured in daily tobacco consumption, number of quit attempts, and health-related quality of life at 6 and 12 months after the intervention. Data will be collected through questionnaires and review of electronic medical records. Cost-effectiveness will be estimated through decision analytic modeling and measured by the incremental cost per quality-adjusted life year.

**Results:**

In the first set of PHC centers participating in the study, eight centers have been included. Recruitment of individual study participants is currently ongoing. Inclusion of a second set of PHC centers is ongoing with expected study start in September 2016.

**Conclusions:**

If TCP is found effective and cost-effective compared to standard treatment, the method could be implemented to facilitate tobacco cessation for socioeconomically disadvantaged groups in the PHC setting in Sweden.

**Trial Registration:**

International Standard Randomized Controlled Trial Number (ISRCTN): 11498135; http://www.isrctn.com/ISRCTN11498135 (Archived by WebCite at http://www.webcitation.org/6kTu6giYQ)

## Introduction

Smoking is a major risk factor for more than 60 different diseases, out of which cardiovascular diseases, lung diseases and cancers are the most common [1]. In Sweden, tobacco use is estimated to cause approximately 12,000 deaths and 100,000 new cases of tobacco-related diseases each year [2], corresponding to 8% of the total disease burden in the country [3]. In addition to the negative effects that tobacco use has on the health and quality of life of the population [4], it is also associated with increased costs for the health care system and for society at large [5]. Currently, 20% of the general adult population in Sweden are daily tobacco users [6]. However, the prevalence of tobacco use is unequally distributed as it is almost twice as high in lower socioeconomic groups compared to higher socioeconomic groups [7].

Since tobacco cessation has been found to reduce the risk of premature morbidity and mortality caused by tobacco-related diseases [8], it is a prioritized area in Swedish public health policy [9]. Treatment guidelines for tobacco cessation in the health care setting have been issued both on the national level in Sweden [1] and the regional level, eg, in Stockholm County [10]. The guidelines recommend that health care providers should offer cessation support to all daily smokers [1]. Although tobacco cessation interventions are one of the most cost-effective interventions available in health care [11], the treatment intensity for tobacco cessation is relatively low in Sweden [12]. In addition, high-risk groups that have an increased need of support are often not reached by such health promoting activities [1]. This could partly be explained by a lower motivation, self-efficacy and social support for quitting, a limited understanding of the harmful effects of tobacco use, and a stronger addiction to tobacco among tobacco users in lower compared to those in higher socioeconomic groups [13]. Other influencing factors include targeted marketing by the tobacco industry and lower adherence to treatment [13]. Moreover, there is a lack of awareness in this target group regarding available treatment options and misconceptions regarding the use and effectiveness of such services [14]. In addition, costs related to seeking and completing treatment for tobacco cessation present particular barriers for socioeconomically disadvantaged tobacco users [14,15]. The need for a more systematic approach and improved access to cessation support for socioeconomically disadvantaged groups has recently been emphasized [16]. There is also a need for more knowledge and training for PHC staff in how to communicate with and empower disadvantaged groups for efficient health promotion [17,18].

Studies conducted on health care consumption in Stockholm in different social groups show that individuals with foreign background, low educational level and low income visit primary health care (PHC) more often than their counterparts [19]. The public has confidence in the health care system [20] and most tobacco users seek care for different health problems at PHC centers. In addition, 87% of patients are positive towards receiving advice on lifestyle changes from health care providers [20]. According to the Swedish Healthcare Act, PHC has the main responsibility for health promotion and disease prevention in the Swedish health care system [21]. Therefore, PHC can be seen as a potential platform to improve the reach of health promoting activities, such as tobacco cessation support, to socioeconomically disadvantaged groups.

In a recent study, the perceived feasibility and optimal design of Tobacco Cessation on Prescription (TCP) as a PHC intervention targeting disadvantaged groups in Sweden, was explored [22]. The study found that TCP was perceived as a useful tool for tobacco users and health care providers and that it could facilitate a more structured and effective approach to tobacco cessation in the future compared to current tobacco cessation practices in PHC [22]. Based on these findings, there is now a hypothesis that TCP could be implemented and prescribed in a similar manner as Physical Activity on Prescription (PAP). PAP has been found effective in changing behavior and improving health and quality of life and is already in use in the PHC setting in Sweden to prevent disease and promote health in the general population [23]. A prescription approach to tobacco cessation could potentially increase the treatment intensity of tobacco cessation in the PHC setting and thus lead to decreased tobacco use and improved health in the target population. The aim of this study is to evaluate the effectiveness and cost-effectiveness of TCP as PHC intervention targeting socioeconomically disadvantaged groups in Stockholm, Sweden.

## Methods

### Study Design

In order to evaluate the effectiveness and cost-effectiveness of the intervention, a two-armed pragmatic cluster-randomized controlled trial [24], with an economic evaluation as a component, has been chosen as the study design. In total, 14-20 PHC centers will be randomized to either intervention or control conditions with a 1:1 ratio. Study participants in the control arm will be offered standard treatment, while study participants in the intervention arm will be offered TCP as a complement to current treatment practices for tobacco cessation at the PHC center. Measurement of patient outcomes will be conducted at baseline and 6 and 12 months after the intervention. The trial has been approved by the Regional Ethical Review Board in Stockholm (ref: 2015/207-31, 2015/1226-32). The study details in this protocol are presented according to the SPIRIT 2013 Statement to ensure high quality in reporting [25]. The study design is presented in Figure 1.

**Figure 1 figure1:**
[figure not shown]
Flow chart of the study design.

### Study Setting and Participants

Study participants will be recruited from participating PHC centers located in socioeconomically disadvantaged areas in Stockholm County, Sweden. Eligible PHC centers will be identified based on a socioeconomic index, which takes into account the income, educational level, ethnicity and health status of the population in a PHC center’s catchment area [26]. Daily tobacco users over 18 years of age with Swedish social security numbers and permanent residence permits, fluent in one of the two most common languages in the study setting, Swedish or Arabic, will be eligible for inclusion in the study. Daily tobacco use will be defined as daily use of cigarettes, snus (smokeless tobacco) or other tobacco products for at least the last year. Ongoing treatment for tobacco cessation and cognitive impairment affecting ability to participate in the study on a voluntary basis will be applied as exclusion criteria.

### Sampling and Recruitment

PHC centers located in areas with low socioeconomic status in Stockholm County will be identified through the previously mentioned socioeconomic index [26], purposively sampled by the researchers and invited to participate in the study. The managers at the PHC centers will be contacted via telephone by the researchers and offered further information via email and a physical meeting before agreeing to participate in the study.

Study participants will be recruited by one to three appointed providers employed at each of the participating PHC centers. However, all staff at the participating PHC centers will be able to refer patients to recruiting staff for more information about the study. In order to reduce selection bias, eligible participants will be identified through a short screening questionnaire before being invited to participate. Further information about the study will be administered by the recruiting staff at the participating PHC centers and written informed consent to participate sought before invited participants will be included in the study. Staff responsible for the recruitment of study participants will receive a brief training in the study design and recruitment procedure before the study start. Recruiting staff will also receive posters to help facilitate the recruitment of individual study participants. The recruitment period is expected to last for 18 to 24 months.

### Interventions

#### Tobacco Cessation on Prescription (Intervention)

The TCP method is based on the PAP concept, which consists of person-centered counseling on physical activity, individualized prescription of physical activity, co-operation between prescribers and providers of physical activity, follow-up of the prescription, and a comprehensive manual that describes for which indications and how the method should be used [27]. In the TCP method, the components in PAP have been adjusted to the tobacco cessation context (see conceptual model in Figure 2 and full description of the core components below). The initial TCP prescription form was drafted by the researchers based on the national guidelines for tobacco cessation treatment in Sweden [1] and the results from the qualitative study that explored the perceived feasibility and optimal design of TCP [22]. The prescription form was then further developed based on an iterative process of feedback from waiting room interviews with patients, as well as workshops and written correspondence with health care providers, researchers and experts on tobacco cessation and lifestyle interventions already available by prescriptions in Sweden. The intervention design was also adjusted based on feedback from PHC providers that pilot tested the TCP method during a 6-week period at a PHC center located in a socioeconomically disadvantaged area in Stockholm.

Prior to the administration of the intervention, one to three PHC providers per center, responsible for the treatment of patients in the intervention group, will receive 4 hours of training by representatives from the Swedish National Tobacco Quitline (SNTQ) [28] and the Stockholm County Council (the regional authority and health care provider) in available treatment options for tobacco cessation and the TCP method. A manual which summarizes the training and describes how the prescription form should be filled out and how it can be used in tobacco cessation counseling, has been developed and will be distributed in connection with the education of PHC providers in the intervention group.

The core components of the intervention consist of tobacco cessation counseling of tobacco users according to the TCP method. This is defined as tobacco cessation counseling (minimum 10 minutes) provided by a qualified health care professional in combination with a prescription for individualized tobacco cessation treatment, including options for (1) further counseling (referral to a health care provider with more competence or SNTQ), (2) pharmacotherapy (nicotine replacement therapy, varenicline, bupropion), (3) other measures for tobacco cessation (physical activity and other strategies to cope with withdrawal symptoms), (4) follow-up (by telephone or revisit) and (5) support for self-management (questions for self-reflection, reference to mobile applications, Web-based counseling and websites for more information and support). The approach will be individualized in the sense that providers will discuss the available treatment options, contraindications, preferences, and other relevant circumstances with the patient and then decide together which treatment alternative(s) suit the individual best. The TCP method also includes follow-up of the prescription by the prescriber on at least one occasion.

#### Standard Treatment (Control)

Standard treatment is defined as treatment for tobacco cessation according to current practices at the PHC center. Since the choice of tobacco cessation treatment varies depending on individual characteristics and preferences of tobacco users and it is up to each PHC center to decide for themselves how their tobacco cessation services should be organized, the treatment components (eg, type of counseling and pharmacotherapy) are expected to vary both within and between the study arms. Thus, the provided treatments will be documented by one to three PHC providers per center in the control group responsible for the treatment of study participants and further defined retrospectively. Since the same treatment components are likely to be present in both study arms, it is important to state that the major difference between them is how the counseling is administered (with or without a prescription form). The minimum intervention for the control group is a brief advice (<5 minutes).

To ensure that the difference between the trial conditions is dependent on the prescription form and not on the training of PHC staff, the PHC providers responsible for the treatment of patients in the control group will receive 3.5 hours of training by representatives from SNTQ and the County Council in available treatment options for tobacco cessation prior to the study start (the same training as the intervention group, excluding the 30 minute TCP component). A manual identical to the one developed for the intervention group, excluding all information about the TCP method and summarizing the training, has been developed and will be distributed in connection with the education of PHC providers in the control group.

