### Sample Size

The required sample size was calculated based on the primary outcome, assuming a 7% rate of 7-day prevalence in abstinence from tobacco use at 6 months follow-up in the control group, significance level of 5% and 80% power to detect a 2.0 relative risk of successful quit attempts in the intervention group compared to the control group. The estimated prevalence of abstinence in the control group corresponds to the success rate of brief advice [33] which is the minimum intervention for the control group in this study. The estimated relative risk corresponds to the relative risk of abstinence from tobacco use for combined pharmacotherapy and counseling, as recommended for the intervention group in this study, compared to minimal intervention or usual care [34]. The unadjusted sample size was found to be 300 per arm. Assuming an intra-cluster coefficient (ICC) of 0.01 according to Adams et al [35] the sample size was adjusted for design effect using the formula: 1 + (m − 1) ρ, where m represents the mean number of participants in each cluster and ρ is the ICC. Having 7 clusters per arm and 43 participants per cluster, the adjusted sample size will be 426 per arm. Finally adjusted for an attrition/drop-out of 8%, the final sample size will be 464 per arm or 928 in total. The estimated attrition rate of 8% is based on reported attrition rates from two other tobacco cessation trials with similar study designs, both conducted in the Swedish health care setting [30,36]. A higher number of participating PHC centers could decrease the required number of study participants without compromising the power to detect a statistically significant difference in the outcomes between the groups at follow-up, wherefore the aim is to recruit a total of 20 PHC centers. A total sample size of 840 would then be needed.

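### The required minimums differ between arms in counselling time and follow-up as well as in the form, so a difference can be credited to the TCP package but not to the prescription form itself

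*Protocol article*

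**What the plan says.** All references are to the protocol article.

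- **Aim.** The Objective in the Abstract is to evaluate "Tobacco Cessation on Prescription (TCP) compared to current practice for tobacco cessation".
- **Intervention.** The subsection Tobacco Cessation on Prescription (Intervention) defines the core as "tobacco cessation counseling (minimum 10 minutes) provided by a qualified health care professional", combined with an individualised prescription. It adds: "The TCP method also includes follow-up of the prescription by the prescriber on at least one occasion".
- **Control.** The subsection Standard Treatment (Control) states: "Standard treatment is defined as treatment for tobacco cessation according to current practices at the PHC center". It expects components to vary within and between arms, and sets a floor: "The minimum intervention for the control group is a brief advice (<5 minutes").
- **Stated contrast.** The same subsection says that "the major difference between them is how the counseling is administered (with or without a prescription form").
- **Stated purpose of the control training.** "To ensure that the difference between the trial conditions is dependent on the prescription form and not on the training of PHC staff", control providers get the same training as intervention providers apart from the 30-minute TCP part: 3.5 hours against 4.
- **Planning effect.** Sample Size works by "assuming a 7% rate of 7-day prevalence in abstinence from tobacco use at 6 months follow-up in the control group", a figure it ties to brief advice. It takes the relative risk of 2.0 from drug treatment plus counselling set against minimal or usual care.

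**The concern.** The control subsection makes a claim about what the randomised comparison isolates: the form is the major difference, and with training matched, the difference depends on the form. The intervention definition requires more than the form. It also requires a minimum counselling time and a follow-up contact, and the control arm has no matching requirement for either.

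Two centres that both follow the protocol could therefore differ in the form, in time with the patient and in number of contacts. Matching the hours of staff training does not match the time or contacts given to patients.

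What is at stake is the label on a positive result. If abstinence is higher under TCP, the between-arm comparison cannot say how much comes from the form and how much from longer counselling or an extra contact, both of which can be given without a form. The Discussion expects the results to inform policy, so a reader who takes the control subsection at its word could credit the form with an effect that the design cannot assign to it.

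**Working it through.** **1. The plan's own figure, and the contrast it rests on.** Inputs from Sample Size: control rate 0.07, relative risk 2.0 (so 0.14), 5% significance (two-sided is my assumption; it reproduces the stated figure), 80% power, ICC 0.01, 43 per cluster, 8% attrition.

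- Unadjusted, pooled normal formula: n = [1.960·√(2·0.105·0.895) + 0.842·√(0.07·0.93 + 0.14·0.86)]² / 0.07² ≈ 300 per arm.
- Design effect: 1 + (43 − 1)·0.01 = 1.42, and 300 × 1.42 = 426 per arm.
- Attrition: 426 / 0.92 = 463.04, rounded up to 464 per arm, or 928 in total.

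The stated size reproduces. (7 clusters of 43 make 301, not 426; that is a separate matter and does not affect this point.) What matters here is the source of the inputs. Brief-advice results in control, and an effect taken from more intensive treatment, describe a contrast in treatment intensity. They do not describe the same counselling with and without a form.

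**2. Required minimums side by side.**

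| Element | TCP arm | Control arm | Equalised? |
|---|---|---|---|
| Prescription form | required | not used | no, by intent |
| Counselling time, minimum | at least 10 minutes | brief advice, under 5 minutes | no |
| Follow-up by the prescriber, minimum | at least 1 | none required | no |
| Staff training | 4 hours | 3.5 hours | yes, apart from the TCP part |

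The ratio of the time floors is 10 / (<5), which is more than 2. Required follow-ups are at least 1 against 0. Three elements differ by requirement; the contrast sentence names one.

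**3. What these figures do not show.** They are floors. Control centres follow current practice, and nothing stops them from counselling for longer or arranging follow-up. The delivered gap may be smaller than the ratio of floors, or it may not. The article cannot settle this. The treatment documentation described under Data Collection can, since it records duration, number of visits and follow-ups in both arms.

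**4. Illustration only.** The documents give no relative risk for the form alone, so the values below are assumptions. With the planned effective 300 per arm and a 7% control rate, two-sided power is:

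| Assumed relative risk | Power |
|---|---|
| 2.0 | 80% |
| 1.75 | 59% |
| 1.5 | 33% |
| 1.3 | 15% |
| 1.2 | 9% |

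If part of the planned doubling came from contact time and follow-up, the trial would not be sized for the remainder. This is no criticism of the size for the package comparison.

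**The case against.** The case on the other side is substantial.

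- **The package is already the target.** The Objective, the Abstract's Conclusions and the end of the Discussion all speak of TCP as a method, and the intervention subsection is open about its time minimum and follow-up. This stands: the stated aim is validly estimated. A reader might infer that the protocol plans to conclude that the form should be implemented by itself; no planned conclusion says so.
- **The control figure is a floor, not a dose.** This stands. A reader might infer that the protocol fixes a larger delivered dose under TCP, or that control patients get under 5 minutes and no follow-up. The documents support neither: control is current practice given by trained staff, and follow-up is not required rather than absent.
- **The text says *major*, not *only*, and the training sentence mainly rules out training as an explanation.** This stands in part. Even so, the sentence names the form as what the difference depends on, and the article gives no reason to rank required time and follow-up below the form.
- **Intensity is part of the hypothesised route.** The Introduction expects a prescription approach to raise treatment intensity, and follow-up belongs to the parent concept. Extra contact prompted by TCP is therefore partly a mechanism and not purely a rival explanation. This supports reading the effect as that of the package; it does not support assigning it to the form.
- **Treatment documentation and a process evaluation are already planned.** This stands, and it keeps the fix cheap. It does not correct the attribution sentence.

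**Conclusion.** The concern holds in a limited form. The statement that matched training makes the difference depend on the prescription form is not supported by the protocol's own definitions, because the required minimums also differ in counselling time (at least 10 against under 5 minutes) and in follow-up (at least 1 against none required).

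Randomisation, the primary analysis and the comparison of TCP as a package with current practice are unaffected. It would go too far to call the trial confounded for its stated aim, or to treat the more than twofold ratio of floors as the delivered difference, which is unknown until documented.

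The conclusion rests on reading the 10-minute minimum and the prescriber follow-up as requirements of TCP, as the intervention subsection presents them, and on the article naming no matching requirement for control. The share of any effect due to the form cannot be identified from the between-arm comparison. The point is about what may be concluded, and it should be settled in the text before results are reported.

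**What to change.** Without changing care in either arm:

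1. Reconcile the intervention and control subsections, so that the description of the contrast lists every element whose requirement differs between arms. Which minimums are appropriate is not a matter for this review.
2. Withdraw the statement that the difference depends on the form. The training sentence can keep its narrower purpose, which is to make training an unlikely explanation.
3. State the contrast and the conclusion as the effect of the TCP package (form, minimum counselling time and follow-up) against current practice.
4. Report delivered counselling minutes, visits and follow-up contacts by arm beside the primary result, from the documentation already planned under Data Collection.
5. Do not rest any claim about the form on an analysis conditioned on delivered contact. Contact arises after randomisation, is affected by arm and probably by motivation, and randomisation does not protect such a comparison. If one is shown, label it descriptive and non-causal.

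The cost is a few sentences, one table from data already being collected, and a narrower claim about the form.
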